#### Cost-effectiveness

##### Effects

The treatment response outcome will be used as an effect measure for the cost-effectiveness analysis. For the cost-utility analyses, both the EQ-5D-5L and the RAND-36 health utilities will be used to compute health gains expressed in quality adjusted life years (QALYs).

##### Cost-effectiveness calculations

We will use the Dutch tariffs (utility weights) for the EQ-5D-5L to calculate the QALYs and the Brazier scoring algorithm (SF-6D) in case we report the RAND-36 data [90, 91]. The area under the curve (AUC) method will be used to calculate the weighted utility of the health states over the full 12-month follow-up period and to calculate QALY gains/losses. Likewise, we will calculate cumulative societal costs over the complete follow-up period based on the cost-estimates that were measured at all follow-up assessments. The cost-effectiveness evaluation will be performed and reported in agreement with the CHEERS statement and we will take the societal perspective in addition to a narrower healthcare costs perspective into account [92]. The incremental cost-effectiveness ratio (ICER) will be calculated by dividing the mean difference in costs by the mean difference in effect, that is: ICER = (Costs intervention – Costs control)/ (Effect intervention – Effect control). Confidence intervals will be estimated around the ICER by using a non-parametric bootstrap approach or other robust measures. Differential costs and effects will be plotted on a cost-effectiveness plane. Furthermore, cost-effectiveness acceptability curves will be drawn and one-way sensitivity analyses aimed at assessing the uncertainty around the main cost drivers will be conducted to assess the robustness of the findings.

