#### Other variables of interest

Various other variables will be assessed. See Table 2 for an overview of all measurement instruments and assessment timepoints.
*Socio-demographic information:* General patient characteristics will be collected at baseline, these include: gender, age, marital status, employment status, education level and ethnicity.*Drinking motives:* Motives for drinking alcohol will be assessed with the Drinking Motives Questionnaire Revised (DMQ-R) [73]. The DMQ-R is widely used for assessing drinking motives among young populations. The 20-item questionnaire assesses motives for drinking on four factors: enhancing (e.g. drinking because it is fun) coping (e.g. drinking to forget worries), confirmative (e.g. drinking to be liked) and social motives (e.g. drinking to be sociable) [74]. The DMQ-R has shown to be acceptable for measuring drinking motives in adults with mood and anxiety disorders and appropriate for Dutch general adult population [74, 75].*General Mental Health:* General mental health is measured with the brief 5-item Mental Health Inventory (MHI-5) [76]. The MHI-5 is a subscale from the MOS SF-36 and has shown to be a good screener for mood disorders in the general population [77].*Patient satisfaction:* Participants’ treatment satisfaction is measured with a Dutch version of the 8-item Zufriedenheid (ZUF-8) questionnaire, scores range between 8 and 32, higher scores indicate more satisfaction with the received treatment [78, 79].*Intervention uptake:* Intervention uptake is measured through log data from the digital alcohol moderation intervention, for example by the number of times participants logged in, the number of completed modules and program duration.*Healthcare utilisation and productivity costs:* Assessment of healthcare costs and productivity losses or gains will be measured with the TIC-P (Trimbos/iMTA questionnaire on Costs associated with Psychiatric illness) a reliable instrument for collecting health care utilization and productivity loss [80].*Anxiety symptoms:* Anxiety symptoms will be measured with the brief 7-item Generalized Anxiety Disorder (GAD-7). Total scores range from 0 to 21, higher scores indicate a higher level of anxiety severity, cut-off points of 5, 10 and 15 indicate levels of mild, moderate and severe levels of anxiety respectively [81]. A meta-analysis has found the GAD-7 to be accurate in identifying generalized anxiety disorder and also any anxiety disorder, with high sensitivity and specificity values when using a cut-off point of 8 [82].*Traumatic events and post-traumatic stress symptoms:* Traumatic events and post-traumatic stress symptoms are assessed with the Dutch Childhood Trauma Questionnaire – Short Form (CTQ-SF) and Post-traumatic Stress Disorder Checklist for DSM-5 (PCL-5) [83, 84]. The CTQ-SF is a 28-item questionnaire that assesses five dimensions of childhood maltreatment: physical abuse, emotional abuse, sexual abuse, physical neglect and emotional neglect [85]. The Dutch CTQ-SF has been found to have adequate internal consistency and reliability. The 20-item PCL-5 questionnaire is widely used to screen for symptoms of post-traumatic stress disorder in the past month [86]. Several studies have found that the PCL-5 has good psychometric properties [84, 86]*Emotion dysregulation:* The widely used Difficulties in Emotion Regulation Scale (DERS-18) will be used to assess difficulties in emotion dysregulation [87]. The DERS-18 is an 18-item short form and has shown good internal consistency and convergent validity in populations with emotional disorders [87].*Resilience:* Psychological resilience will be measured with the brief Dutch 9-item Resilience Evaluation Scale (RES). The RES measures two constructs underlying resilience, that is self-confidence and self-efficacy. The instrument is used in various studies and has shown good psychometric properties [88].*Borderline personality features:* The 24-item Personality Assessment Inventory-Borderline Features (PAI-BOR) scale will be used to assess borderline features. The PAI-BOR questionnaire screens for borderline personality disorder features [89].*Perceived impact of COVID-19 measures:* We used a self-constructed 7-item questionnaire to assess the impact of COVID-19 and related measures on the participants’ depressive symptoms, alcohol use and study participation. The questions assess to what extent the pandemic led to either an increase, decrease or had no impact on depressive symptoms and alcohol consmption and what the reasons for the in-or decrease were. One question assessed whether the pandemic and restricting measures had an influence on any attempts of reducing alcohol use. Lastly, two questions assessed whether the pandemic had any influence on study participation and if so, for which reasons.

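### The printed ICER formula is a plain difference in arm means and names no baseline covariate, although baseline utility and baseline costs are collected

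*Protocol article*

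**What the plan says.** All of this is in the protocol article. Under Cost-effectiveness calculations, the ICER "will be calculated by dividing the mean difference in costs by the mean difference in effect", and the ratio is then written out as intervention minus control in both numerator and denominator. For QALYs, "The area under the curve (AUC) method will be used to calculate the weighted utility of the health states over the full 12-month follow-up period". For costs, the plan takes "cumulative societal costs over the complete follow-up period based on the cost-estimates that were measured at all follow-up assessments". On uncertainty: "Confidence intervals will be estimated around the ICER by using a non-parametric bootstrap approach or other robust measures". For robustness, "one-way sensitivity analyses aimed at assessing the uncertainty around the main cost drivers will be conducted".

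The Effects section makes treatment response the outcome of the cost-effectiveness analysis and QALYs the outcome of the cost-utility analysis. Neither economic section names a covariate. The only covariates named in Data analysis are the randomisation strata, and those are for the effectiveness mixed models. Table 2 schedules EQ-5D-5L, RAND-36 and TIC-P at baseline and at 3, 6 and 12 months.

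**The concern.** The area-under-the-curve QALY has baseline utility as its first point, and people with low utility at entry tend to have low utility later. If the arms differ in baseline utility by chance, a plain difference in mean QALYs carries that difference along, partly through the first point and mostly through the later visits. Regression on the baseline value removes this component and the variance that goes with it.

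What is at stake is the precision of the cost-utility ratio, the cost-effectiveness plane and the acceptability curves, and how far the observed QALY difference reflects who was randomised where. The planned one-way sensitivity analyses vary cost drivers, so they would not reveal this.

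**Working it through.** **The plan's own figure.** The economic sections give no SD, correlation or expected QALY gain. The only figure to reproduce is the sample size, which supplies the number per arm. For 50% against 25%, two-sided alpha 0.05 and power 0.80, the arcsine effect size is h = 0.5236, which gives 57.26, so 58 per arm and 116 in total. Then 116 × 1.35 = 156.6, in agreement with the stated 156. With 1:1 allocation that is 78 per arm.

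**Inputs.** From the article: visits at 0, 3, 6 and 12 months, and 78 per arm. Assumed, because the article gives neither: utility SD 0.20 (range 0.15 to 0.30), and the same correlation ρ between any two visits, 0.5 (range 0.3 to 0.7).

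**Weights.** The trapezoid rule at 0, 0.25, 0.5 and 1 year gives 0.125, 0.25, 0.375 and 0.25, which sum to 1.

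**Slope of the QALY on baseline utility.** 0.125 + 0.875ρ. At ρ = 0.5 this is 0.5625.

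**Chance imbalance.** The SE of the baseline difference is 0.20 × √(2/78) = 0.032. An imbalance of one SE shifts the QALY difference by 0.5625 × 0.032 = 0.018. Of this, only 0.125 × 0.032 = 0.004 comes from the direct weight; the rest comes through correlation with later visits.

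**Precision.** The QALY variance is SD² × [(1 − ρ)Σw² + ρ], with Σw² = 0.28125.
- At ρ = 0.5 this is 0.04 × 0.6406 = 0.0256, so the unadjusted SE is √(0.0256 × 2/78) = 0.0256.
- R² on baseline is 0.5625²/0.6406 = 0.49, so adjustment multiplies the variance by 0.506.
- The adjusted SE is 0.0256 × √0.506 = 0.0182.

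For SD 0.20 and 78 per arm:

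| ρ | Slope | Shift from one-SE imbalance | SE unadjusted | SE adjusted | SE reduction |
|---|---|---|---|---|---|
| 0.3 | 0.39 | 0.012 | 0.0226 | 0.0189 | 16% |
| 0.5 | 0.56 | 0.018 | 0.0256 | 0.0182 | 29% |
| 0.7 | 0.74 | 0.024 | 0.0284 | 0.0157 | 45% |

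Over SD 0.15 to 0.30 and ρ 0.3 to 0.7, the one-SE shift runs from 0.009 to 0.035, the unadjusted SE from 0.017 to 0.043 and the adjusted SE from 0.012 to 0.028. The percentage reduction does not depend on the SD or on the number per arm. With 58 per arm (SD 0.20, ρ = 0.5) the SEs are 0.0297 and 0.0211.

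**Definition of the QALY outcome.** The article speaks of QALY gains or losses without saying whether this is the total area or the change from baseline. If it is change, baseline gets weight 0.125 − 1 = −0.875, and the slope at ρ = 0.5 becomes 0.5625 − 1 = −0.4375, so an unadjusted difference would shift the other way. In a linear regression with baseline utility as covariate, subtracting baseline from the outcome lowers the baseline coefficient by exactly 1 and leaves the arm coefficient unchanged. The adjusted result is therefore the same under either definition.

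**Costs.** The cumulative total is described as the sum over follow-up assessments, so baseline TIC-P costs are not a term in it. They act only through correlation with later costs. The article gives no cost SD or correlation, so no size can be computed.

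**The case against.** The strongest reply is that the sentence is the generic definition of an ICER. A regression-adjusted mean difference satisfies it too, nothing rules adjustment out, and a condensed article may leave the covariates to a fuller plan. This stands in part. A reader might infer that the sponsor has decided against adjustment, but the article never says so, and the option of other robust measures leaves room. What remains is that a specific formula is printed, that it is unadjusted as written, and that a better one is available at no data cost.

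Second, under randomisation the plain difference is unbiased, and chance imbalance is part of the sampling error that the bootstrap represents. This is correct, so the point is not bias. The bootstrap displays that error, however; it does not reduce it.

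Third, the economic analysis is secondary, and the sample size was set for treatment response. That limits the weight of the point but does not remove it.

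Three stronger readings are also tempting:
- *Imbalance is as large as any plausible QALY gain and so decides the sign of the ICER.* The article states no expected QALY gain, so there is nothing to compare with.
- *Baseline costs are counted in the outcome as baseline utility is.* They are not part of the stated follow-up sum.
- *The QALY argument affects every ICER.* It applies to the cost-utility ratio only, because the cost-effectiveness ratio uses treatment response.

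**Conclusion.** The point holds as an improvement to a printed estimator. As written, the formula is an unadjusted difference in arm means, while the baseline measures needed to improve it are already collected. For the cost-utility analysis, an unadjusted QALY difference would remain unbiased on average. It would move by about 0.018 for a one-SE baseline imbalance, and its SE would be 0.026 where 0.018 is attainable. A 29% lower SE is worth nearly twice the sample size for this outcome (1/0.506 = 1.98).

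These figures rest on an assumed utility SD of 0.20, an equal correlation of 0.5 between visits and 78 per arm with complete data. The SE reduction is 16% at a correlation of 0.3 and 45% at 0.7. For costs, only the direction of the argument can be given, not its size.

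**What to change.** State in Cost-effectiveness calculations that:
- incremental QALYs are the arm coefficient from a regression on arm, baseline utility (from the same instrument) and the randomisation strata;
- incremental costs are the arm coefficient from a regression on arm, baseline TIC-P costs and the strata;
- both models are refitted within each bootstrap replicate, on the same resampled participants so that the correlation between costs and effects is kept;
- the ICER, the plane and the acceptability curves are formed from these adjusted differences.

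Also say whether the QALY outcome is the total area or the change from baseline, although the adjusted arm effect is the same. If a fuller plan already specifies this adjustment, one sentence aligning the formula with it is enough. The cost is wording and a few lines of analysis code; no data collection or sample size changes.

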### Data management

Every included study participant will be given an unique project number for de-identification purposes. The de-identification key will only be accessible for principal investigators, data managers and research assistants of the project. Data collection and management will be conducted with Castor EDC [58]. Data in Castor EDC is stored on servers in the Netherlands and complies with the European General Data Protection Regulation (GDPR) and complies with Good Clinical Practice guidelines. The digital alcohol moderation intervention will be accessible for study participants by logging in on the digital intervention with a personal account. The program and user data from the digital intervention are hosted on a European cloud service provider and complies with the GDPR and other security standards (ISO 27001, NEN 7510). Study outcomes will be anonymously analysed and reported.

## Discussion

Co-occurring depressive disorders and problematic alcohol use are associated with various adverse health outcomes [11–13]. An add-on digital alcohol moderation intervention to depression treatment could be an acceptable and effective treatment for young adults with co-occurring depressive disorders and problematic alcohol use. Currently, availability and evidence on (cost-) effectiveness of such treatment for young adults is insufficient. The current RCT addresses this research gap by evaluating the (cost-) effectiveness of simultaneously adding a digital alcohol moderation intervention to depression treatment (TAU), compared to TAU among young adults with co-occurring depressive disorders and problematic alcohol use. We expect to find a 50% treatment response in the intervention group and a 25% treatment response in the control group. Furthermore, we expect larger improvements in secondary outcome measures and cost-effectiveness in favour of the intervention group.

The current study has several strengths and challenges. Our trial is designed as a pragmatic RCT and aims to evaluate the (cost-)effectiveness of the add-on digital alcohol moderation intervention to treatment as usual for depressive disorders. Pragmatic trials often have higher external validity and generalizability because of conducting the trial in normal clinical practice settings and by using less strict in-and exclusion criteria. Such trial designs therefore often have lower internal validity compared to traditional explanatory RCTs [93]. However, a pragmatic trial design is the most suitable design considering our research aim and the economic evaluation that is conducted alongside the trial. Other strengths of the current study include a multi-centre RCT design, a 12-month follow-up, a relatively large sample size, insight in the (cost-)effectiveness of the combined alcohol and depression treatment for young adults and lastly a novel digital add-on alcohol moderation intervention that was developed through co-creation with expert patients and based on a former and existing web-based alcohol self-help which was found effective among problem drinkers [59]. A common challenge in the field of digital interventions is poor treatment adherence and high dropout rates [94]. Literature shows that guidance can enhance adherence and increase effectiveness compared to completely unguided digital interventions [32, 94]. Thus, minimal asynchronous adherence-focused guidance will be provided by a coach, who will be available for questions and will motivate users to complete the alcohol moderation modules after certain periods of inactivity in the program. Additionally, automatic e-mail reminders will be sent to users after inactivity in the digital intervention. Study drop-out is prevented by giving participants a monetary compensation for every completed follow-up assessment. Completion of follow-up assessments is facilitated by giving participants the opportunity to fill out questionnaires online and on any mobile device. Another challenge for the current study is the COVID-19 pandemic and the corresponding restricting measures that were taken by the Dutch government, such as lockdowns and social distancing. Preliminary research suggest that the COVID-19 pandemic and the restricting measures influence, both negatively and in some circumstances positively, alcohol use and depressive symptoms [95–100]. Therefore, they might also influence the outcomes of the current study. In order to assess the perceived impact of these COVID-19 related measures on both alcohol use and depressive symptoms of study participants, we have added COVID-19-specific items to our online assessments.

If the add-on digital alcohol moderation intervention to TAU for depressive disorders proves to be effective for young adults with co-occurring depressive disorders and problematic alcohol use, dissemination and implementation of the combined treatment in mental health care should be considered. Jellinek, a Dutch health care facility specialized in addiction, is committed to take up the management of the digital alcohol moderation intervention after the research project is finished with acceptable results. This could contribute to sustainable implementation of the digital alcohol moderation intervention in mental health care practice.

## Data Availability

The data that support the findings of this study are available from Arkin but restrictions apply to the availability of these data, which were used under license for the current study, and so are not publicly available. Data are however available from the authors upon reasonable request and with permission of Arkin.

## Abbreviations

AUC: Area Under the Curve
AUD: Alcohol User Disorder
AUDIT: the Alcohol Use Disorder Identification Test
BtB: Beating the Booze
CBT: Cognitive Behavioural Therapy
CES-D: Center for Epidemiological Studies-Depression questionnaire
CTQ-SF: Childhood Trauma Questionnaire – Short Form
DERS-18: Difficulties in Emotion Regulation Scale
DMQ-R: Drinking Motives Questionnaire Revised
EQ-5D-5L: five-level and five-dimensional EuroQol
GAD-7: Generalized Anxiety Disorder questionnaire
GDPR: European General Data Protection Regulation
ICER: Incremental Cost-Effectiveness Ratio
MHI-5: Mental Health Inventory
MI: Motivational Interviewing
PAI-BOR: Personality Assessment Inventory-Borderline Features scale
PCL-5: Post-traumatic Stress Disorder Checklist for DSM-5
QALYs: Quality Adjusted Life Years
RAND-36: RAND-36 item Health Survey
RCT: Randomized Controlled Trial
RES: Resilience Evaluation Scale
TAU: Treatment As Usual
TIC-P: Trimbos/iMTA questionnaire on Costs associated with Psychiatric illness
TLFB: Timeline Followback
ZUF-8: Zufriedenheid questionnaire
